### Interventions

Subjects enrolled in this study are randomized in equal proportions between sonification and sham-acoustics, receiving either training for the upper extremities with real-time movement sonification (intervention group) or training with sham-acoustics (control group). During the intervention phase, subjects of both groups receive movement therapy for the upper extremities at 4 days per week for 3 weeks, i.e., a total of 12 sessions. A therapy session takes 30 min. Within each study therapy session, gross motor arm movements are performed focusing on (a) reaching, (b) grasping, (c) bimanual activities, and (d) velocity. Exercises belonging to those categories are performed in blocks of 5 min. An exercise catalog can be used by the therapists containing ideas for arm movements of each category. Content and repetitions are recorded for later analysis. A break and a short calibration of the XSens system is scheduled between the 5-min blocks. Subjects of both groups wear the sonification system (straps, sensors, head phones, on-body controller) during the therapy.

Once a patient is enrolled in the study, the study site makes every reasonable effort to follow the patient for the entire study period. If study sessions are canceled due to indisposition of the patient or the therapist, or due to technical issues, one additional session per week can be scheduled. The intervention period should not exceed 3 weeks. Adherence to therapy is monitored by documenting therapy failures, therapy durations, and drop-outs.

The following individual criteria were defined for discontinuing the allocated intervention: incidence of a new disease or complication of the underlying disease, which makes continuation of the study impossible, and at the patients' request or at request of the legal representative. Patients who discontinue the intervention are considered *off intervention* and follow the same schedule of measurements as patients who finished the intervention. Discontinuation of the intervention is not a reason for withdrawal from the study. Patients are free to withdraw from the study for any reason at any time. The investigator also may withdraw patients from the study to protect their safety or if they are unwilling and unable to comply with the study procedures.

All patients included in the study are inpatients at the rehabilitation hospital and receive the normal therapy setting during the study period. The only intervention which is prohibited during the intervention period is robot-assisted training for the upper extremities.

### Arm motion tracking and sonification

Arm movements are tracked with a mobile motion capture system (MTx miniature 3DOF inertial orientation tracker; Xsens Technologies BV, Enschede, The Netherlands). It contains seven inertial sensor units, which are composed of three accelerometers, three gyroscopes, and magnetic sensors allowing measuring three dimensional orientation. All sensors are connected by cable with an on-body controller (XBus Master) worn at a belt which transmits synchronized sensor data (50 Hz) wirelessly to a laptop (Bluetooth protocol 2,400–2,500 MHz). Sensors are fixated by velcro straps and aligned to seven body parts representing a kinematic chain (sternum, shoulders, upper and lower arms). By comparing orientation of two interconnected sensors and considering predefined segments' lengths it becomes possible to determine joint angles and calculate relative joint positions based on forward kinematics (43), here the relative wrist position in relation to the intersection of shoulder axis and spine of a biomechanical upper body model.

Wrist position is calculated in spherical coordinates, i.e., each posture is determined by the azimuth angle, the elevation angle as well as the radial distance between wrist and origin of the spherical coordinate system (Figure 1). These data are submitted to the open source software applications PureData and CSound for sonification. The sonification concept is inspired by ecological relationships between sound and energy like it is given for the sound amplitude, which is usually determined by the amount of energy being transformed by the sound-emitting event: The harder a tennis player hits the ball with the racket, the louder the impact boom will sound (20). Such ecological relations are well established within the hearing system and the perceptual generation of such kind of auditory information does not need conscious attention. The sonification technique is based on frequency modulation of a synthesized sound with a sawtooth wave form. The carrier frequency, which is the basic frequency, is set to 200 Hz for the left arm and to 300 Hz for the right arm when the arms are hold in a neutral position besides the body (elevation angle 0°). Arm elevation increases sound frequency by a maximum of 200 Hz, which is achieved when both arms are stretched above the head (elevation angle 180°). The azimuth angle determines the panning (equal power panning) and thus the interaural intensity difference. Radial amplitude modifies the perceived brightness of the sound by a logarithmic change of the frequency regulation index between 0 and 0.15. Finally, the absolute velocity of the wrist defines the sound amplitude and thus the loudness. Higher velocities result in higher sound amplitudes. Thus, right and left arm movements produce and modify one sound each which are provided to the patients of the experimental group wirelessly via headphones. Notably, no sound can be heard when the arms are at rest. The control group is provided with sham-acoustics. Arm movements produce the sound of ocean waves, which are not altered by the movement trajectory.

**Figure 1 F1:**
[figure not shown]
Loci of the sensors (gray boxes) at patients' upper body. Sensor data are fused to calculate spherical coordinates of the wrist in a reference frame with origin at the upper body, i.e., the intersection between spine and shoulder axis. Four parameters are mapped onto sound: the angle between gray vector and sagittal plane (azimuth angle), the angle between vector and horizontal plane (elevation angle), vector length (radial amplitude), and absolute velocity of the wrist.

The volume of the movement sonification and the sham-acoustics is adapted according to the patients' preference (maximal 65 decibel).

### Outcomes

Primary outcome measure is the Box and Block Test (44). The test is a measure of unilateral gross manual dexterity. It counts the number of wooden blocks that can be transported from one compartment of a box to another compartment within 1 min. The Box and Block test shows high test-retest and interrater reliabilities in elderly subjects and subjects with neurological disorders (45, 46). The construct validity of the test is high when compared with the ARAT and the Fugl-Meyer test (45, 46). The Box and Block test is suitable to detect changes over time in stroke patients (47).

Secondary outcome measures are the Action Research Arm Test (ARAT) and the Stroke Upper Limbs Capacity Scale (SULCS). The ARAT assesses mainly the ability to handle smaller and larger objects with a variety of qualitatively rated items. It includes four subtests: grasp (6 items), grip (4 items), pinch (6 items), and gross movement (3 items). The scores for each item range from 0 to 3. We use the standardized protocol published by Yozbatiran et al. (48) to assess the ARAT. The test shows high intrarater reliability and interrater reliability. Validity is high when compared to the Fugl-Meyer test and it is sensitive to detect changes (47).

The SULCS assesses the capacity of the paretic upper limb in stroke patients. It consists of 10 items which represent tasks that are related to daily activities (49). The items assess proximal arm capacity without need for active wrist or finger movement (3 items), arm capacity combined with basic hand capacity (grasp tasks without manipulating, 4 items), and advanced hand capacity (manipulating tasks, 3 items). The scale has good interrater reliability and a high construct validity when compared with the ARAT and the Rivermead Motor Assessment (RMA) (50).

All these outcome measures are assessed at baseline before the start of the intervention, at post-test after the last intervention, and at follow-up test 2 weeks after the end of the intervention. The measures are assessed by an assessor blind to treatment allocation. The assessor is experienced and trained in performing the clinical assessments.

Differences between baseline and post measurement, and between baseline and follow-up measurement will be calculated for all outcome measures to determine short-term and long-term changes. These changes will be compared between groups. The primary and secondary outcome measures will be presented as means and standard deviations or as medians and 25th and 75th percentiles for each group.

### Participant timeline

The study timeline shown in Table 1 presents an overview of the time schedule of enrolment, interventions, and assessments of the outcome measures.

**Table 1 T1:** Time schedule of enrolment, interventions, and assessments.

	**Enrolment**	**Allocation**	**Post-allocation**		
**TIMEPOINT**		**0**	**Baseline**	**Post**	**Follow-up**
ENROLMENT:					
Pre-screening	X				
Eligibility screening	X				
Informed consent	X				
Allocation		X			
Randomization		X			
INTERVENTIONS:					
Movement sonification					
Sham-acoustics					
ASSESSMENTS:					
Box and Block Test			X	X	X
Action Research Arm Test			X	X	X
Stroke Upper Limbs Capacity Scale			X	X	X

### Sample size

The sample size calculation for this trial is based on the pilot study by Schmitz et al. (34) investigating the feasibility of movement sonification in stroke patients. The study found a small, but statistically significant effect and a high correlation between the number of blocks which were transported in the Box and Block test before and after five 20-min sessions with movement sonification. As the intervention period is much longer in this trial, we assume a medium effect. For an effect size of *f* = 0.2, a correlation among repeated measures of 0.7, a power of 80%, and a significance level of α = 0.05 a total sample size of 26 subjects is required. The sample size calculation was performed using G^*^Power.

A dropout rate of 20% was anticipated, consequently a minimum number of 32 subjects has to be enrolled in the study.

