The goal of the intended clinical trial is to prove the impact of a novel method for arm movement sonification in motor rehabilitation after stroke. The method provides real-time feedback about three-dimensional wrist movements in relation to the trunk. Auditory feedback informs about the angular direction of movements in the horizontal and vertical plane, the radial amplitude as well as the absolute velocity of the wrist. Accordingly, each movement produces an unequivocal sound which represents additional sensory feedback. We hypothesize that patients benefit from the real time feedback during movements with the impaired arm due to the structural equivalence of the sound to movement information from other modalities which can amplify activity of multisensory integration areas in the brain, support motor control and substitute partially lost proprioception as indicated by Scheef et al. (21), Schmitz et al. (22), Effenberg et al. (28) and Danna and Velay (29). A pilot study with a precursor version of this method provided encouraging results as four stroke patients showed improved performance in the Box and Block test after five training sessions (34). Furthermore, a related method has recently been applied in a randomized controlled clinical trial by Scholz et al. (42). After an exploration-phase, stroke patients learned to play simple melodies by moving their impaired arm in 3D-Cartesian space. Ten training sessions of 20 min each with this musical sonification reduced pain according to the pain-score of the Fugl-Meyer test, enhanced hand functions as assessed by the Stroke Impact Scale and increased smoothness of reaching as shown by kinematic analyses. Effect sizes were moderate. The present approach differs from the method presented in Scholz et al. (42) mainly by the way arm movements are sonified and by capturing the whole upper body. This allows providing intuitive feedback for both arms while controlling for upper body movements. Thus, the present method prospects even larger effects.

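### The 80% power is attached to a medium effect, but f = 0.2 with correlation 0.7 implies a between-group difference in change of about 0.85 SD; at 0.5 SD the power is about 35%

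*Protocol article*

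**What the plan says.** The Sample size section starts from a pilot study that it describes as having found a small but significant effect, with a high correlation between Box and Block counts before and after five sessions. It continues "As the intervention period is much longer in this trial, we assume a medium effect". The inputs are "For an effect size of *f* = 0.2", "a correlation among repeated measures of 0.7", 80% power and "a significance level of α = 0.05", and the result is that "a total sample size of 26 subjects is required", computed in G*Power. The section does not say which effect f describes, or what difference in blocks or in SD units it stands for.

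The Theoretical approach section describes the pilot: "four stroke patients showed improved performance in the Box and Block test after five training sessions". It mentions no comparison group.

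The Abstract, the end of the Outcomes section and the Statistical methods section agree on the question: change from baseline in the sonification group compared with change in the sham group. The primary outcome is analysed by repeated measures analysis of variance, with measurements at baseline, post-test and follow-up.

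**The concern.** An f for a repeated-measures interaction is not a standardised difference between groups. When the correlation enters separately, f is the spread of the interaction effects across the cells, in units of the SD of one measurement. Those cell effects are each only a fraction of the difference in change between the groups, so a modest-looking f can stand for a large difference.

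A reader of the section will conclude that the trial has an 80% chance of finding a medium benefit over sham. If the 80% belongs to a much larger benefit, a null result would be read as evidence against an effect that the trial was unlikely to detect. The rationale has the same weakness. The pilot effect is a before-after gain, which also contains practice and spontaneous recovery. In this trial both groups receive the same therapy time and usual rehabilitation, so those components occur in both groups and cancel in the comparison.

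**Working it through.** **Inputs.** From the Sample size section: f = 0.2, correlation ρ = 0.7, α = 0.05, N = 26. From Trial design: two groups, 1:1, so 13 per group. From Outcomes: three measurements. That m = 3 was entered in the software is inferred. SD below means the SD of a single Box and Block measurement unless stated otherwise.

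**1. Reproducing N = 26.** Within-between interaction, sphericity assumed: λ = N·m·f²/(1 − ρ), with df (m − 1) and (N − 2)(m − 1).
- m = 3, N = 26: λ = 26 × 3 × 0.04 / 0.3 = 10.4, df 2 and 48, power 80.6%. N = 25 gives 78.8% and N = 24 gives 76.9%, so 26 reproduces.
- m = 2, two-sided 0.05: N = 26 gives 71.5%; N = 32 is needed.
- m = 2, one-sided 0.05: N = 26 gives 81.9%.
- Within-factor (time) test, m = 3: also N = 26, but it tests change over time, not the group difference in change.
- Between-factor test: 160 to 170.

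**2. What f = 0.2 means as a group difference in change.** Let δ be the difference in change from baseline.
- Sustained effect, pattern (0, δ, δ): the pattern has mean 2δ/3, so the deviations are −2δ/3, δ/3, δ/3. Each group carries half of these, with opposite signs. The mean square is (4 + 1 + 1)δ²/(9 × 4 × 3) = δ²/18. So f = δ/√18 and δ = 0.2 × 4.243 = 0.85 SD.
- Linear build-up, pattern (0, δ/2, δ): f = δ/√24, so δ = 0.98 SD at follow-up.
- Baseline and post only: f = δ/4, so δ = 0.80 SD.

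SD of the change score = √(2 × (1 − 0.7)) = 0.775. So 0.85 SD is 1.10 change-score SD, and 0.80 SD is 1.03.

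**3. Power with 13 per group.** The change-score column is a two-sided two-sample t test, with noncentrality (δ/0.775) × √(13/2) and 24 df. The omnibus column is the three-measurement test with a sustained effect.

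| δ (SD) | Change score | Omnibus |
|---|---|---|
| 0.50 | 35.2% | 35.9% |
| 0.80 | 71.5% | 75.5% |
| 0.85 | 76.5% | 80.6% |
| 0.90 | 81.1% | 85.2% |

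For δ = 0.5 the noncentrality is 0.6455 × 2.550 = 1.65.

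**4. Sensitivity at 0.5.**
- Linear build-up, omnibus: 28%.
- 0.5 measured in change-score SD: 23%.
- Baseline-adjusted analysis (residual SD √(1 − 0.49) = 0.714): 40%.
- All 32 enrolled patients complete: 42% (change score) to 44% (omnibus).
- 80% power on the change score at 0.5 SD would need 39 completers per group (38 give 79.3%).

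**The case against.** The strongest reply is that the label is not wrong on the scale to which the protocol attaches it. The usual medium value of f is 0.25, so 0.2 is slightly below medium, and f = 0.25 in the same test would have 95% power with 26 patients. The benchmark of 0.5 SD appears nowhere in the article. This stands as far as it goes: the conflict appears only once f is converted to a difference in change. That is nevertheless the quantity the trial sets out to compare, and by the same conversion f = 0.25 would be 0.25 × √18 = 1.06 SD.

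A second reply is that the calculation that was run is unknown. This also stands in part: a one-sided two-measurement test and the within-factor test also lead to 26. The first would put f = 0.2 at 0.80 SD, which is still large. Under the second, f would not describe a group difference at all, and the 80% would not apply to the comparison of interest. Neither rescues the medium label for that comparison.

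Third, the Theoretical approach section cites a randomised trial of a related method with moderate effects and expects larger ones here. But the Sample size section bases its assumption on the pilot alone and plans on medium. It presents the effect as an assumption and does not claim that the pilot demonstrated a group difference.

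Finally, an article may leave the software's test family and scaling options to the full protocol, so their absence is no fault.

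A reader might infer that 26 is a miscalculation. The documents do not support that, because the number follows from the stated inputs.

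**Conclusion.** The point holds as a fault in the label and justification of the assumed effect. In the three-measurement interaction test that reproduces 26, the 80% belongs to a sustained between-group difference in change of about 0.85 SD (1.10 change-score SD), or 0.98 SD at follow-up if the effect builds linearly. For the baseline-to-post contrast alone, f = 0.2 (0.80 SD) has about 71% power at two-sided 0.05, and 80% needs about 0.9 SD. At 0.5 SD the power is about 35%.

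This rests on m = 3 (inferred), sphericity, equal variances, the stated correlation of 0.7, 13 completers per group, and 0.5 SD as the meaning of medium, which is an outside convention. It would go too far to say that the article itself defines medium as 0.5 SD, or that the trial's power is 35% outright: the true effect is unknown, and 35% is the power at that one value.

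**What to change.** Leave N at 26 completers and rewrite the paragraph:
- Drop the label of a medium effect.
- State that 26 completers give about 80% power for a sustained between-group difference in Box and Block change of about 0.85 SD of a single measurement in the three-measurement omnibus test, or about 0.9 SD for baseline-to-post change. A range reaching down to 0.8 SD should not be given as having 80% power: it has 71% (change score) to 75% (omnibus). If another test was run, say so and give the matching difference.
- Add that power for a difference of 0.5 SD is about 35%.
- Say that the pilot's small before-after effect, described without a comparison group, does not by itself support a between-group effect of this size.
- Say that a non-significant result will not exclude a moderate benefit.

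The cost is wording only. Design, recruitment and primary analysis do not change, but the stated sensitivity of the trial becomes less favourable.

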### Recruitment

In the pre-screening, a scientific staff member determines on a daily basis all stroke patients admitted to the hospital. These patients are screened for eligibility by the study coordinator. Patients who fulfill all inclusion and exclusion criteria are approached with the study information. If the patient is interested in the study and agrees to participate, written informed consent is obtained. If the patient has a legal representative, the study information is also provided to the legal representative and he gives written informed consent. Patients who are not yet, but potentially may become eligible, are followed by the study coordinator until they meet all the eligibility criteria.

### Allocation

Patients included in the study are randomly assigned to either the control or the experimental group with a 1:1 allocation as per a computer generated randomization schedule stratified by age (<60 and ≥60 years) and lesion side (left and right sided) using blocks of random sizes. The block sizes will not be disclosed to ensure concealment. The randomization schedule will be concealed until the primary endpoint will be analyzed. The allocation is done by a scientific staff member not directly involved in the project. The staff member sends a form with the allocated intervention to the therapist who is not involved in assessing the outcome measures.

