### Statistical methods

Descriptive statistics including means and standard deviations or medians and 25th and 75th percentiles for continuous data, and frequencies for categorical data will be determined. The appropriateness of the randomization will be examined by testing for between group differences in demographical and clinical variables (e.g., age, time since stroke, SULCS score).

Among the cases available for analyses, intention-to-treat analyses will be performed. For all outcome measures, the within-subject differences between the baseline and post-test, and the baseline and follow-up test are of central interest in the intervention group compared to the control group. For the primary outcome measure, a repeated measures analysis of variance will be used. Pairwise comparisons will be generated using Tukey's method. A subgroup analysis will be performed to investigate the influence of lesion side. For the secondary ordinal outcome measures, non-parametric statistics will be used. Between-group comparisons (intervention vs. control group) will be performed to compare the short-term changes (baseline—post-test) and long-term changes (baseline—follow-up) between groups using Mann-Whitney *U*-tests. In addition within-group comparisons will be performed using Friedman tests. If the Friedman test showed significant differences, Wilcoxon matched-pairs tests will be used to compare baseline and post, and baseline and follow-up measures. Effect sizes (r) of changes between groups and within-groups will be calculated.

In addition, a per protocol analysis will be done, excluding patients who deviated from the protocol. Missing data will be replaced by the last value carried forward method.

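### The named tests compare changes from baseline and adjust for neither the baseline score nor the stratification factors, which costs precision; the planned baseline significance tests cannot judge the randomisation

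*Protocol article*

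**What the plan says.** Under Allocation, the 1:1 randomisation is "stratified by age (<60 and ≥60 years) and lesion side (left and right sided) using blocks of random sizes", which makes four strata.

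Under Outcomes, differences from baseline to post-test and from baseline to follow-up are formed for every measure, and "These changes will be compared between groups".

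Under Statistical methods, the primary outcome (Box and Block) is analysed by repeated measures ANOVA, with the within-subject differences from baseline as the focus. For ARAT and SULCS, which the article calls ordinal, short-term changes and "long-term changes (baseline—follow-up) between groups using Mann-Whitney" tests are planned. No covariate or stratum term is named for any of these. Lesion side comes back only as a subgroup analysis; the age stratum does not come back at all.

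The same section adds: "The appropriateness of the randomization will be examined by testing for between group differences in demographical and clinical variables".

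**The concern.** There are three parts.

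- **Baseline score.** An ANOVA that takes baseline as one of the repeated responses tests the difference in change between groups. It subtracts the whole baseline value, whereas with a correlation of 0.7 and equal variances the best linear correction subtracts 0.7 of it. The extra noise widens the interval. In any one trial with a chance baseline difference, the change score also over-corrects.
- **Stratification factors.** Stratifying and then leaving the factors out of the model gives a standard error that does not reflect the balance the design created. If the factors are prognostic, the test is conservative.
- **Baseline tests.** Under proper randomisation every baseline difference is due to chance, so a significance test of it cannot show whether the randomisation was appropriate.

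For ARAT and SULCS there is also an inconsistency: rank methods are chosen because the scales are ordinal, yet scores are subtracted before ranking.

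At stake is precision in a very small trial, using data that will be collected anyway.

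**Working it through.** **Inputs (Sample size section).** "For an effect size of *f* = 0.2"; "a correlation among repeated measures of 0.7"; "a power of 80%, and a significance level of α = 0.05"; and "a total sample size of 26 subjects is required", so 13 per group. Outcomes gives three measurement times.

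**1. The plan's own figure.** For the group-by-time interaction (2 groups, m = 3 times, sphericity), λ = f²·N·m/(1−ρ) = 0.04 × 26 × 3/0.3 = 10.4 on 2 and 48 degrees of freedom. Power is 0.806, and N = 24 gives 0.769. The stated 26 reproduces.

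**2. Error variance of the baseline-to-post contrast, equal variances σ².**

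- Change score: 2(1−ρ)σ² = 2 × 0.3 = 0.60σ².
- Baseline-adjusted: (1−ρ²)σ² = 1 − 0.49 = 0.51σ².
- Ratio: (1+ρ)/2 = 0.51/0.60 = 0.85, a 15% reduction.

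**3. Allowance for chance imbalance.** Estimating the baseline slope inflates the adjusted variance on average by about 1 + 1/(N−4) = 1 + 1/22 = 1.045. Net ratio at ρ = 0.7: 0.85 × 1.045 = 0.889, a gain of about 11%.

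| ρ | Reduction before allowance | Net of chance imbalance |
|---|---|---|
| 0.7 | 15% | 11% |
| 0.8 | 10% | 1 − 0.90 × 1.045 = 6% |
| 0.9 | 5% | 1 − 0.95 × 1.045 = under 1% |

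**4. Power for this one contrast at N = 26.**

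- Effect implied by f = 0.2 with two times: λ = 0.04 × 26 × 2/0.3 = 6.93. Setting this equal to δ² × (26/4)/0.60 gives δ² = 0.64, so δ = 0.80 SD.
- Change score: λ = 6.93 on 1 and 24 df, power 0.715.
- Baseline-adjusted, ignoring imbalance: λ = 0.64 × 6.5/0.51 = 8.16 on 1 and 23 df, power 0.781.
- Baseline-adjusted, with the allowance: λ = 8.16/1.045 = 7.80, power 0.763. With two stratum terms (21 df) it is 0.759. Both round to 76%.

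**5. Size of a chance imbalance.** The probability of a baseline difference of at least 0.5 SD in either direction is 2(1−Φ(0.5/√(2/13))) = 0.20. Given a difference of 0.5 SD, the change-score estimate moves by (1−0.7) × 0.5 = 0.15 SD.

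**6. Stratification factors.** The document gives no correlation of age or lesion side with outcome, so no gain can be computed. As an assumption only: if the strata explained 5%, 10% or 20% of the variance of change, the actual two-sided level would be about 2(1−Φ(1.96/√(1−R²))) = 0.044, 0.039 or 0.028.

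**The case against.** The strongest reply is that nothing here is invalid. Under randomisation the change-score comparison is unbiased, ignoring the strata errs on the conservative side, and N = 26 was calculated for the unadjusted test, so design and analysis agree. The article is also a condensed protocol, and a fuller plan may name covariates. The first part stands and limits the point to efficiency. The second does not remove it: the article does not leave the tests open but names them, and as named they carry no adjustment.

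The size is also open to challenge. The 15% needs ρ = 0.7, and the Sample size section describes the pilot correlation only as high. At 0.9 almost nothing is left. That objection stands, which is why a range is given.

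A reader might draw four stronger conclusions that the document does not support:

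- *That the 15% is the cost of omitting baseline, age and lesion side together.* It comes from the Box and Block baseline alone, for one contrast, and says nothing about the Mann-Whitney tests.
- *That the trial has only 71% power.* That figure is for a two-time comparison; the planned three-time interaction test has 80.6%.
- *That the baseline tests replace adjustment or decide whether to adjust.* The article gives them another purpose and attaches no decision to them.
- *That imbalance is otherwise unhandled.* Randomisation is stratified, change scores do use the baseline value, and a lesion-side subgroup analysis is planned. None of these, however, is covariate adjustment of the main comparison.

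**Conclusion.** The point holds as one of efficiency, not of bias or invalidity. The named analyses leave out baseline and stratification variables that will already be in the database. For the Box and Block baseline-to-post contrast, baseline adjustment is worth 15% of the error variance at ρ = 0.7, about 11% net of chance imbalance, and raises power on that contrast from about 71% to about 76%. This assumes equal variances over time, a linear relation with baseline, 26 analysed patients and the 0.80 SD effect implied by f = 0.2. The gain shrinks as ρ rises. The contribution of age stratum and lesion side is unknown; if they are prognostic, leaving them out makes the test conservative.

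The criticism of the baseline tests rests on none of these figures. As worded, they cannot deliver what the article says they are for.

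**What to change.** In Statistical methods:

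- **Box and Block:** analyse the post-test and follow-up scores with one baseline-adjusted model, either a mixed model or ANCOVA. Name the choice in advance and include group, baseline Box and Block score, age stratum and lesion side.
- **ARAT and SULCS:** replace the Mann-Whitney tests on raw changes by rank ANCOVA with the baseline score and the two strata. With 26 patients this is safer than a proportional-odds model, given that ARAT has 19 items scored 0 to 3 (a range of 0 to 57).
- **Baseline:** delete the significance tests and report baseline characteristics descriptively by group.

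The planned 26 need not change for this. The cost is a change of wording, three model degrees of freedom (baseline score, age stratum, lesion side) and no new data. It should be made before the allocation is revealed for analysis.
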